**Additional information**	
Demographics	Children’s age, gender, grade (primaries 1–6), ethnicity (Han or others), parental educational level (below college; college or above) and yearly household income (low: RMB < 84,000; medium: RMB 84,000 – 132,000; high: RMB > 132,000) [60] will be reported by parents

In addition, the collection of all indicators at the four-time points will follow the following process. Day 1–7: Demographic information (filled by parents) and ActiGraph 3X + measured PA, sedentary behavior, and sleep; Day 8: anthropometric and body composition measures and FMSs; Day 9: physical fitness assessment; and Day 10: psychological outcomes. The Day 8–10 data collection will be implemented by four trained student helpers with assistance of PE teachers in an elementary school gymnasium, where the temperature will be constant at 20℃ and humidity will be controlled at 50% during the assessment.

### Data analysis

Quantitative data analyses will be performed using SPSS and Mplus. Descriptive statistics of all continuous variables will be expressed as mean ± standard deviation (*M* ± *SD*). Independent samples *t*-tests and Chi-square tests will be employed for checking the randomization, analyzing the dropout, and detecting the potential confounders at baseline. Intention-to-treat approach will be used for the primary analyses, with per-protocol analyses as sensitivity tests. Missing data will be imputed using a multiple imputation approach with linear and logistic regression equations. The statistical significance level will be set to *p* < 0.05 (two-tailed). Generalized linear mixed models (GLMM) will be used to evaluate the intervention effects on outcome measures, with time, condition, and the interaction of time and condition as fixed effects, adjusting for baseline values. Post-hoc tests will be conducted where a significant interaction effect is detected by using the least significant difference method. In addition, structural equation modeling will be used to analyze the interrelationship (e.g., mediation mechanisms) of outcomes, using a bias-corrected bootstrap approach (5000 resamples). For the qualitative data, a thematic analysis approach will be applied using NVivo 11 software.

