#### Randomization and blinding

To avoid the potential for contamination, randomization will be conducted at the school level. All eligible schools will be randomly assigned to one of the two groups prior to baseline assessment, where each group will consist of three schools. Each school will select 28 obese children from four classes covering grades 2–5 to participate in this study, and the children in the same school will receive the same treatment. Randomization will be implemented with a ratio of 1:1, using the Excel software by a researcher who will not be involved in the participant recruitment, data collection or evaluation. Due the ethical concerns, participants are not able to be blinded as they will be informed with the study purpose and group allocation in the written informed consent form. Intervention facilitators and outcome evaluators will be concealed for the group allocation.

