### Implementation evaluation

This study will use the Reach, Effectiveness, Adoption, Implementation, and Maintenance (RE-AIM) framework [74, 75] to assess the implementation of FMSPPOC among obese children. Details can be found in Table 3.

**Table 3 Tab3:** The RE-AIM framework of implementation evaluation for the FMSPPOC program

Element	Program phase	Quantitative measures	Qualitative measures
**Reach**	Pilot study	1. The number of target participants who are willing to participate in the pilot study ● 20 obese children from a weight loss center for children and adolescents in Shijiazhuang, China	1. Identify the feasibility of recruiting enough eligible participants 2. Identify the barriers for recruitment and enrolment 3. Identify the facilitators and barriers for obese children 4. Identify the reasons for participants dropout 5. Identify the strategies for improving the adherence
	Main study	1. The number of target participants who are willing to participate in the main study ● Expected: 168 obese children from six primary schools of three districts (Yu-Hua, Chang-An and Xin-Hua; two schools per district) in Shijiazhuang, China	
**Effectiveness**	Main study	1. What proportion of participants completes the intervention? ● To ensure more than 85% participants completing the intervention program	1. Explore the experience of participating in the program from participants’ views 2. Identify the conditions and circumstances that influence the intervention effectiveness 3. Identify the reasons that result in the variations/differences in the intervention effects across participants within the program 4. Identify the potential contamination for the intervention effectiveness 5. Count numbers of sports injuries and other unintended consequences during the intervention period, and analyze the reasons
		2. How do completers compare to non-completers? ● Dropout analysis will be conducted to identify the baseline difference between completers and dropouts ● Sensitivity test will be conducted to identify the impact of the dropouts on the evaluation of the intervention effects	

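### Baseline significance tests are the only stated way to find covariates beyond the baseline outcome; a short list should be fixed in advance instead

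*Protocol article*

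**What the plan says.** Under Data analysis, the protocol article gives two-sample t-tests and chi-square tests three jobs: "Independent samples *t*-tests and Chi-square tests will be employed for checking the randomization, analyzing the dropout, and detecting the potential confounders at baseline". The significance level in the same section is 0.05, two-tailed. The intervention effect comes from a generalized linear mixed model "with time, condition, and the interaction of time and condition as fixed effects, adjusting for baseline values". No other covariate is named.

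The trial does collect candidate covariates. The Demographics row of Table 4 lists "Children’s age, gender, grade (primaries 1–6), ethnicity (Han or others), parental educational level (below college; college or above) and yearly household income". The Introduction also names the moderating role of demographics among the objectives.

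Under Randomization and blinding, whole schools are allocated, three per arm, and "Each school will select 28 obese children from four classes covering grades 2–5 to participate in this study".

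The article does not say what follows from a significant or a non-significant baseline test.

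**The concern.** A baseline test between randomised arms asks whether chance could have produced the observed difference. If allocation was done properly, chance did produce it, so the p-value says nothing useful about whether the randomisation worked. Nor does it pick out the variables worth adjusting for. That depends on how strongly a variable predicts the outcome, which the test never looks at. A strong predictor with a moderate imbalance can pass unnoticed, while an irrelevant variable can be flagged.

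Two features of this design sharpen the problem. The arms are made of three schools each, so socioeconomic differences between arms are likelier than with 168 individually randomised children. The tests named are also independent-samples tests on children, which ignore allocation by school and so flag too readily.

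At stake are an adjusted model whose content is settled only after the baseline data are seen, some lost precision, and a shift in the estimate when a moderate imbalance in a predictor goes unflagged.

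**Working it through.** **Inputs from the protocol article.** Three schools per arm with 28 children each (Randomization and blinding) give 3 × 28 = 84 per arm, which agrees with the 84 per condition in Sample size estimate. Alpha is 0.05 two-sided (Data analysis). The planned effect is d = 0.54 and the ICC 0.01 (Sample size estimate). The article gives no ICC for any covariate and no covariate-outcome slope, so values for these are assumptions; 0.01 is borrowed from the sample size calculation. The point disputes no stated figure; 84 per arm only sets the resolution of the baseline tests.

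**1. What the test can flag.** The smallest observed standardised difference that reaches p < 0.05 is t(0.975, 166) × √(2/84) = 1.974 × 0.1543 = 0.305 SD. Anything smaller is not flagged. For a binary covariate near 50%, the matching figure is 1.96 × √(2 × 0.5 × 0.5/84) = 1.96 × 0.0772 = 0.151, or about 15 percentage points.

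**2. How often it flags under school allocation.** The variance of an arm difference is inflated by 1 + 27 × ICC. The false-positive rate of a test that ignores this is 2 × [1 − Φ(1.96/√(1 + 27 × ICC))].

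| Covariate ICC | Inflation | False-positive rate |
|---|---|---|
| 0 | 1.00 | 5% |
| 0.01 | 1.27 | 8.2% |
| 0.05 (assumed) | 2.35 | 20% |
| 0.10 (assumed) | 3.70 | 31% |

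**3. How often a near-threshold imbalance goes unflagged.** The SD of an arm difference is √(2 × inflation/84): 0.154, 0.174, 0.237 and 0.297 for the four rows above. The probability that the observed difference lies between 0.25 and 0.305 SD is 2 × [Φ(0.305/SD) − Φ(0.25/SD)]. This gives about 6%, 7%, 9% and 10% per covariate.

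**4. What such an imbalance does to the estimate.** The shift is imbalance × slope. Assume 0.2 to 0.4 SD of outcome per SD of covariate, beyond what the baseline outcome already explains. The shift then runs from 0.25 × 0.2 = 0.05 to 0.30 × 0.4 = 0.12 SD, which is 9% to 22% of d = 0.54. It applies only in the 6-10% of trials in step 3.

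**5. Precision.** Assume a covariate effect of 0.3 and a residual SD of 0.7. With no residual school variance, always adjusting gives an SD of the estimate of about 2 × 0.7/√168 = 0.108. For a covariate evenly spread over schools, never adjusting raises the variance by (0.49 + 0.09)/0.49 = 1.18. Test-then-adjust should fall between the two, and simulation agrees:

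- No residual school variance: SD 0.115-0.116 for test-then-adjust against 0.108-0.110 for always adjusting, so (0.115/0.108)² = 1.13 and (0.116/0.110)² = 1.11. A second simulation gave 0.112-0.117 against 0.106-0.112.
- School SD of 0.1: 0.140-0.142 against 0.135-0.137, so (0.140/0.135)² = 1.08.

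Allowing for the spread across settings, test-then-adjust has roughly 5-15% more variance. Type I error was near 5% under both strategies.

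**The case against.** The strongest reply is that the article contains no harmful rule. It does not say that a non-significant test shows the arms to be comparable, or that a variable with p ≥ 0.05 is shut out of the model. A reader might infer both, but the text supports neither, and a fuller covariate list may sit in an analysis plan that is not shown. This stands, and it limits the point to the use of the tests that the article does state. Checking randomisation and detecting confounders by t-test and chi-square test is a method fixed in words, not a detail left out.

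A reader might also infer that the important predictors are missing from the model. That is too strong. The baseline value of the outcome, probably the best single predictor, is adjusted for. Every school supplies classes from grades 2-5, so age and grade should be close to balanced; leaving them out costs mainly precision. Bias is likelier from socioeconomic variables.

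The size is modest too. The shift in step 4 is conditional and uncommon for any one covariate, the slopes are assumed, type I error holds, and residual school variance shrinks the relative gain. All of this stands.

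Finally, one might extend the criticism to dropout, since the same tests are named for it. Table 3 says only that "Dropout analysis will be conducted to identify the baseline difference between completers and dropouts", which is ordinary description. The article also plans intention-to-treat analysis, multiple imputation, per-protocol analyses and a sensitivity test for the impact of dropouts. No conclusion of no difference is planned, so dropout is not part of this point.

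**Conclusion.** The point holds in a limited form. Significance tests at baseline are the wrong instrument for certifying randomisation or choosing covariates, and they are the only stated route to a covariate beyond the baseline outcome. The screen errs both ways: it is blind below 0.305 SD, whatever the prognostic strength, and it flags about 8% of the time at ICC 0.01 and 20% at an assumed 0.05, where 5% is intended. The first figure follows from the stated sample size alone. The others rest on the covariate ICC.

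The consequence is a covariate set that depends on the data, roughly 5-15% more variance under an assumed covariate effect of 0.3, and some bias given the observed imbalance. Type I error is not materially affected. The documents do not support saying that non-significance will be read as comparability, or that prognostic covariates are excluded as a rule. The point is modest in size, and worth acting on because the remedy is nearly free.

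**What to change.** In Data analysis, remove the randomisation check and the confounder search from the uses of t-tests and chi-square tests. Describe baseline balance by arm with means or percentages and standardised differences.

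Name the covariates of the primary mixed model in advance and use them whatever imbalance is observed: the baseline value of the outcome, age or grade, sex, and one socioeconomic variable (household income or parental education). The demographic ones are already collected under Demographics in Table 4. Keep the list at child level and short, since six schools leave almost no room for school-level covariates. The comparison of completers with dropouts may stay as a descriptive step.

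The cost is a change of wording and a few child-level degrees of freedom out of 168 children. No new data are needed, and the stated sample size, power and alpha do not change.

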**Methods:**

Using a cluster randomized controlled trial (CRCT), 168 Chinese obese children (8–12 years) from 24 classes of six primary schools will be recruited and randomly assigned to one of two groups by a cluster randomization, including a 24-week FMSPPOC intervention group and a non-treatment waiting-list control group. The FMSPPOC program includes a 12-week initiation phase and a 12-week maintenance phase. School-based PA training sessions (2 sessions/week, 90 min each session) and family-based PA assignments (at least three times per week, 30 min each time) will be implemented in the initiation phase (semester time), while three 60-min offline workshops and three 60-min online webinars will be conducted in the maintenance phase (summer holiday). The implementation evaluation will be undertaken according to the RE-AIM framework. For intervention effectiveness evaluation, primary outcome (FMSs: gross motor skills, manual dexterity and balance) and secondary outcomes (health behaviors, physical fitness, perceived motor competence, perceived well-being, M-PAC components, anthropometric and body composition measures) will be collected at four time-points: at baseline, 12-week mid-intervention, 24-week post-intervention, and 6-month follow-up occasions.

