## Method

### Study design

This study will apply a two-group double-blinded cluster randomized controlled trial (CRCT) with four measurement occasions, including baseline assessment (T0), mid-intervention assessment (T1: 12 weeks after the baseline assessment), post-intervention assessment (T2: 24 weeks after the baseline assessment), and follow-up assessment (T3: 48 weeks after the baseline assessment). Two groups include: 1) an intervention group (IG), receiving the FMSPPOC intervention for 24 weeks; and 2) a waiting-list control group (WCG), receiving the FMSPPOC intervention or relevant materials (based on participants’ requirements) after the completion of all data collection for IG (see Fig. 1). The design, implementation, and reporting of the FMSPPOC will follow the SPIRIT guidelines and the CONSORT statement [54, 55] (Supplement Material 1). The study protocol was approved by the Research Ethics Committee of Hebei Normal University (ref. No.2021LLSC051). This study was a key part of a large research project funded by the National Social Sciences Funding Committee of China (Ref. No.: 19200526).

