**Implementation**	Pilot study & Main study	1. Is the intervention delivered as intended? ● Using a process evaluation framework to assess the fidelity and quality of intervention implementation (e.g., exercise intensity will be monitored during the intervention; a fidelity evaluation scale will be used) ● Trained research staff observe teachers’ implementation of the FMSPPOC program (e.g., percent of lesson content conveyed, whether lessons will be presented in recommended order) and parents’ involvement in the family-based PA assignments ● Using self-reported e-logs to assess the participants’ satisfaction with the intervention implementation ● Using a self-reported scoring sheet to assess the consistency in delivering the intervention and evaluate the consistent commitment of facilitators and collaborators	1. Identify the acceptability, adaptability, and practicality of the intervention 2. Identify any modifications that have been done during the intervention process, and explore the reasons behind them 3. Identify the barriers that influence the fidelity of the intervention 4. Identify the potential facilitators and barriers that influence the intervention implementation and provide strategies to address them in the future
		2. Did participants adhere to the intervention program? ● Analyses for the attendance rate of each session and overall completion rate ● Check the completion of the family-based PA assignment by self-reported e-logs ● Self-reported e-logs completed by the intervention facilitators and collaborators	
**Maintenance**	Main study & Follow-up	1. The extent to which the intervention outcomes are sustained ● Data analyses for the sustained intervention effects during 6-month follow-up	1. Identify the components that influence the successful sustainability of the current program 2. Identify the modifications made to sustain the current program 3. Identify the facilitators and barriers of seeking more collaborators in future 4. Identify the facilitators and barriers that maintain the program and promote the program to a wider population in future

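### Table 3 promises a sensitivity test for the impact of dropout, but the only sensitivity test the plan names is per-protocol analysis, which does not test the assumption made about children who leave

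*Protocol article*

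**What the plan says.** The Protocol article, Data analysis, sets the analysis populations in one sentence: "Intention-to-treat approach will be used for the primary analyses, with per-protocol analyses as sensitivity tests". On missing outcomes it adds: "Missing data will be imputed using a multiple imputation approach with linear and logistic regression equations".

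Table 3 (Implementation evaluation, Effectiveness row) makes two promises about children who leave. The first is descriptive: "Dropout analysis will be conducted to identify the baseline difference between completers and dropouts". The second concerns the effect estimate: "Sensitivity test will be conducted to identify the impact of the dropouts on the evaluation of the intervention effects". Table 3 gives no method for the second, and Data analysis names no sensitivity test other than per-protocol. Neither place defines the per-protocol set.

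The Abstract describes the comparator as "a non-treatment waiting-list control group". Study design says that these children are offered the programme or its materials only "after the completion of all data collection for IG". Adherence is tracked for the programme, in the Implementation row of Table 3, through "Analyses for the attendance rate of each session and overall completion rate" and through logs of the home assignments.

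**The concern.** A sensitivity test for dropout should ask how far the result would move if the children who left did worse, or better, than the primary analysis assumes. Regression-based multiple imputation, as described, assumes that a child who leaves would have scored like a similar child who stayed. Per-protocol analysis leaves that assumption alone and changes who is counted. If it is the only check, a per-protocol result close to the intention-to-treat result could be reported as robustness to dropout when dropout was never examined.

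The second issue is balance between arms. Only the intervention arm has sessions, home assignments and workshops to attend. Removing poor attenders would compare a selected intervention group with an unselected control group, and the difference between them would no longer rest on randomisation alone.

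**Working it through.** **1. Purpose against method.** Table 3 states a purpose (the impact of dropouts on the effect) and no method. Data analysis states a method (per-protocol) and no purpose beyond being a sensitivity test. The completer-versus-dropout comparison by t-tests and chi-square tests describes who left at baseline and does not re-estimate the effect. So nothing in the article varies the assumption about missing outcomes.

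**2. Inputs from the article (Sample size estimate).** Planned effect d = 0.54; attrition 15%. The attrition figure fits the stated size: 12 classes × 6 children = 72 per arm, and 72 / 0.85 = 84.7, against 84 stated. Nothing below depends on this.

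**3. Assumed inputs.** The share excluded as non-adherent, f, is set at 15% to match the attrition allowance and the Table 3 target of more than 85% completing. The correlation r between adherence and outcome is not given. It is taken as what remains after the planned adjustment for baseline, with values of −0.3, 0, 0.3 and 0.5.

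**4. Exclusion in the intervention arm only.** If the least adherent share f is removed, mean adherence among those kept rises by φ(z_f) / (1 − f), and the estimated effect shifts by

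shift = r × φ(z_f) / (1 − f).

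For f = 0.15, φ(z_f) / (1 − f) = 0.274.

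| r | shift (SD) | estimate if the true effect is 0.54 |
|---|---|---|
| −0.3 | −0.08 | 0.46 |
| 0 | 0 | 0.54 |
| 0.3 | 0.3 × 0.274 = +0.08 | 0.62 |
| 0.5 | 0.5 × 0.274 = +0.14 | 0.68 |

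A simulation with one million children per arm gave the same figures. The positive shifts appear also when the true effect is zero. When the same selection acts in both arms the shift is about 0. Because r is taken after baseline adjustment, the unit is the SD of the adjusted outcome; in raw SDs the shift would be smaller.

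**5. Why agreement would not be reassuring.** Suppose the effect among stayers is 0.54, 15% of intervention children leave and keep none of the benefit, and leavers are otherwise like stayers (r = 0). The effect over all randomised children is then 0.54 × 0.85 = 0.46. Imputation from stayers returns about 0.54, and per-protocol also returns about 0.54. The two agree, and both miss the loss. A delta adjustment would show it: lowering the imputed scores of intervention leavers by δ moves the effect by −0.15 × δ, and δ = 0.54 gives −0.08.

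**The case against.** The strongest objection is that joining Table 3 to the Data analysis sentence is the reader's own step. Data analysis does not mention withdrawal when it names per-protocol, and Table 3 names no method. This is right, and it limits the point: the article does not say that per-protocol is the dropout test. It promises a dropout test and names only one kind of sensitivity test, which would not serve.

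A reader might also infer that per-protocol can remove only intervention children and is therefore bound to favour the programme. The documents do not support that. The per-protocol set is undefined; it could drop control children for missed assessments, ineligibility or contamination, which Table 3 says will be looked for. If it were a completer analysis, children would leave from both arms, and equal selection gives a shift of about zero. The direction also depends on a correlation that the article does not give, and baseline adjustment removes part of any advantage of children who were already more skilled. The introduction offers some support for a positive correlation, since it says that poor motor skills may weaken motivation for activity, but this is not evidence on adherence in this trial. An excluded share well above 15% would have no source in the article.

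Finally, definitions of analysis sets and departures from the imputation assumption are commonly left to an analysis plan, and one may exist. That answers a complaint about missing detail. It does not fully answer this one, because the article states a purpose and the only method it names does not fit it. Under either reading of per-protocol, adherence-based or completer-based, the imputation assumption stays untested.

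**Conclusion.** The point holds in a limited form. As written, the plan has no analysis that would show what dropout did to the effect, although Table 3 promises one; this follows from the text and needs no numerical assumption. Exclusions based on attendance or completion would fall on the intervention arm and break the randomised comparison. This would probably favour the programme if better-performing children adhere more: +0.08 to +0.14 SD under the assumed 15% exclusion and correlations of 0.3 to 0.5. Neither the sign nor the size is established by the documents. The fault lies in a supporting analysis; the primary intention-to-treat result does not depend on it.

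**What to change.** In Data analysis, describe per-protocol as a supplementary analysis of adherence, no longer as a sensitivity test, and define its set by arm. For the test promised in Table 3, name a delta-adjusted multiple imputation: the imputed outcomes of leavers are shifted by a pre-stated range of amounts, separately by arm, and the effect is re-estimated at each. Include as one scenario a control-based imputation, in which intervention children lost to assessment are imputed from the control group's course.

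The cost is a few sentences and a little extra analysis, with no new data. The sensitivity estimate may be less favourable than a per-protocol one.

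### Six schools are randomised, but the plan's only stated cluster is the class and the GLMM names no school term; if school is left out, the 5% error rate is not held

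*Protocol article*

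**What the plan says.** On allocation, the protocol article (Randomization and blinding) is clear: "randomization will be conducted at the school level", "each group will consist of three schools", and "the children in the same school will receive the same treatment". On size it says "Each school will select 28 obese children from four classes covering grades 2–5 to participate in this study".

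The Sample size estimate section uses a different cluster. It takes the class as the unit, with 6 children per class, an ICC of 0.01 and 12 clusters per arm (24 in all), and arrives at 84 children per arm.

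The Data analysis section gives the effect model: "Generalized linear mixed models (GLMM) will be used to evaluate the intervention effects on outcome measures, with time, condition, and the interaction of time". The interaction is with treatment arm, all three terms are fixed, and the model adjusts for baseline. The section mentions no random effect, covariance structure, cluster-robust error or degrees-of-freedom method. On missing data: "Missing data will be imputed using a multiple imputation approach with linear and logistic regression equations". Alongside independent-samples t-tests, "Chi-square tests will be employed for checking the randomization, analyzing the dropout, and detecting the potential confounders at baseline". School is mentioned in none of these.

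**The concern.** Every child in a school receives the same treatment, so each comparison between arms is a comparison between schools, and there are only six of them. Variation between schools therefore goes straight into the error of the treatment effect. A model that omits it gives standard errors that are too small and p-values that are too optimistic for the primary outcome.

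A condensed article may leave the random-effect structure to a fuller document. Here, however, the article does state a clustering unit, and it is the class. Someone completing the unnamed part of the model from this text could reasonably choose class, or child because of the repeated measurements. Neither carries school variance.

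Two lesser matters go with this. The baseline and dropout tests treat children as independent, and one stated purpose of those tests is to detect confounders. The imputation equations are described without saying whether school enters them.

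**Working it through.** **The plan's own figure first.** Inputs from Sample size estimate: d = 0.54, two-sided alpha 0.05, power 80%, class size 6, ICC 0.01, attrition 15%.

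- Unclustered n per arm = 2 × (1.960 + 0.842)² / 0.54² = 53.8, so 54 (55 with the t distribution).
- Class design effect = 1 + (6 − 1) × 0.01 = 1.05, giving 56.7 to 57.8.
- Attrition: dividing by 0.85 gives 67 to 68 per arm.
- 68 / 6 = 11.3, so 12 classes per arm. The cluster count reproduces. The 84 does not follow directly, since 12 × 6 = 72 (84 is 12 × 7). That mismatch is a separate matter. What counts here is that only class clustering was allowed for.

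**Type I error if school is omitted.** Inputs from Randomization and blinding: 3 schools per arm, 28 children per school (7 per class); after 15% attrition, 28 × 0.85 = 23.8. The article gives no school-level ICC. Applying its 0.01 to schools is an assumption, and so are the values 0.02 to 0.10.

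Design effect DE = 1 + (m − 1) × ICC. Type I error with children as units = 2 × [1 − Φ(1.96 / √DE)].

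- ICC 0.01, m = 28: DE = 1.27; 1.96 / √1.27 = 1.739; error 8.2%.
- ICC 0.05, m = 28: DE = 2.35; 1.96 / √2.35 = 1.279; error 20.1%.

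The last two columns are from 20,000 simulated null trials per setting (6 schools × 4 classes × 7 children, single outcome).

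| School ICC | Children as units, m = 28 | Children as units, m = 23.8 | Class means, 22 df | School means, 4 df |
|---|---|---|---|---|
| 0 | 5.0% | 5.0% | 5.0% | 5.2% |
| 0.01 | 8.2% | 7.7% | 7.5% | 5.0% |
| 0.02 | 11.4% | 10.4% | not run | not run |
| 0.05 | 20.1% | 18.0% | 15.0% | 5.0% |
| 0.10 | 30.8% | 27.9% | 21.8% | 5.0% |

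Simulation with children as units and m = 28 agrees with the formula: 8.4%, 20.2% and 31.0% at ICC 0.01, 0.05 and 0.10. With 6 children per class (24 per school), class means reject in about 7% of null trials at ICC 0.01 and 14.2% at 0.05.

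**Repeated measures.** With three follow-up times and a child random intercept only, the time-by-condition F-test rejected in 9.3% of simulated null trials at an assumed school-by-time ICC of 0.01, and in 28.9% at 0.05. These simulations do not include the baseline adjustment.

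**Power once school is carried.** Noncentrality = 0.54 / √(2 × DE / N), with N per arm = 3m and 3 + 3 − 2 = 4 df.

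- ICC 0.01, m = 28, N = 84: 0.54 / √(2 × 1.27 / 84) = 3.11; power 65%.
- ICC 0.01, m = 23.8, N = 71.4, DE = 1.228: 0.54 / √(2 × 1.228 / 71.4) = 2.91; power 60%.
- ICC 0.05: 42% and 39%.
- ICC 0: 75% and 68%, so the few degrees of freedom alone take power below 80%.

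**The case against.** The strongest reply is that silence is not error. A generalised linear mixed model has random effects by definition, and the sentence lists only the fixed ones. The article calls the trial cluster randomised throughout and says outright that schools are randomised. A fuller protocol or analysis plan may name a school effect and a degrees-of-freedom method. This stands, so the inflation is conditional on school being left out. It does not remove the point, because the article states a clustering unit of its own and that unit is not the one randomised.

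Other limits also stand:

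- A reader might infer that imputation is single-level. The text names only the type of regression equation, and such equations can include school.
- A reader might infer that covariates found significant at baseline will be added to the model. The article says only that potential confounders will be detected; the adjustment it states is for baseline values.
- Baseline tests that ignore clustering can mislead the balance check. They do not set the type I error of the primary comparison.
- The only ICC in the article is 0.01, at which the inflation is modest. The larger figures rest on assumed ICCs and on calculations without baseline adjustment.

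**Conclusion.** The point holds in conditional form. The article randomises six schools, sizes the trial on 24 classes, and describes a model with no school term. If the fitted model carries only child or class, the nominal 5% test has a true size of about 8% (child) or 7% (class) when the article's ICC of 0.01 applies to schools. At an assumed school ICC of 0.05 it is about 18–20% or 14–15%. The ranges reflect 24 to 28 children per school. If school is carried with suitable degrees of freedom there is no such inflation: the comparison of school means on 4 df stayed at 5% at every ICC simulated.

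The document does not support the stronger reading that the planned analysis excludes school and that its error rate therefore exceeds 5%. The defect is that the primary inference depends on a term the article leaves open, while its one cue on clustering points to the wrong level.

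**What to change.** In Data analysis:

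- State that the GLMM includes a random intercept for school, with class nested in school and child nested in class, and uses Kenward-Roger or Satterthwaite degrees of freedom.
- Add a comparison of the six school means on 4 df as a check. An exact permutation test cannot fill this role: with 20 possible 3-versus-3 allocations, its smallest two-sided p-value is 2/20 = 0.10.
- Include school in any imputation model.
- Do not use independent-samples significance tests at baseline to select confounders. Pre-specify any covariates beyond the baseline value of the outcome.

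Reconcile Sample size estimate with Randomization and blinding on what the cluster is.

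Replacing multiple imputation by a likelihood analysis, or choosing particular covariates such as sex and grade, is a matter of preference and not required by this point.

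The wording change is small, but its consequence is not. Confidence intervals will be wider, and power for d = 0.54 will be about 60–65% at a school ICC of 0.01, lower at larger ICCs, against the planned 80%. The sponsor should know this before the analysis is fixed.
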